**Methods:**

A triple-masked, randomized, placebo-controlled trial will be conducted in adults with clinically active CD. Participants (*n* ≤ 32) will be randomized to either 24 mg encapsulated XN per day or placebo and followed for 8 weeks. Throughout the trial, participants will be queried for adverse events. Biomarkers of clinical safety, blood and stool markers of inflammation, platelet function, Crohn’s Disease Activity Index score, stool microbial composition, and XN metabolite profiles in blood, urine, and stool will be assessed every 2 weeks.

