### Strategies to improve adherence to interventions {11c}

Adherence will be monitored throughout the trial at weekly visits through verbal query and formally assessed at the week 4 and closeout visits by capsule count. Participants will be provided with sufficient study product for 5 weeks (35 capsules) at randomization and week 4 in anticipation of potential scheduling changes and/or unexpected losses. Participants will be considered adherent by taking >80% of expected doses throughout their participation in the trial. Participants will be provided suggestions to improve adherence such as daily phone alarms, consistent timing, reminder notes, etc. Returned study product will be stored in a locked cabinet in a locked room for future quality assessment.

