### Outcomes {12}

The primary outcomes of the phase II trial include changes in laboratory toxicology measures, vital signs (blood pressure and heart rate), and AEs (Table 1). Assessment of laboratory measures to determine safety includes review for new-onset abnormalities (confirmed with repeat testing at the following clinical visit or as soon as possible following closeout, as applicable), including new-onset clinically significant elevation of liver function tests [aspartate transaminase (AST), alanine transaminase (ALT), bilirubin or alkaline phosphatase], new-onset anemia, elevations in creatinine, and/or reductions in estimated glomerular filtration rate (eGFR). Elevations of liver function tests will be considered “significant” if (1) abnormal per laboratory reference ranges and (2) represent a 25% deviation from previously observed values. New-onset anemia will be considered “significant” if (1) hemoglobin < 14 g/dL (140 g/L), hematocrit < 42% (< 0.42), or RBC < 4.5 million/mcL (< 4.5 × 10^12^/L) (for men); or hemoglobin < 12 g/dL (120 g/L), hematocrit < 37% (< 0.37), or RBC < 4 million/mcL (< 4 × 10 ^12^/L) (for women); *and* (2) values represent a 10% change or more from *baseline* values; *and* (3) values remain abnormal with repeat testing within 2 weeks. This threshold reduces reporting of new “borderline” abnormal values for participants with “high normal” baseline values. For elevations of creatinine, “significant” will be evaluated as greater than a 20% increase from *baseline* values, whereas reductions in eGFR will be considered as “significant” if greater than a 20% decrease from *baseline* values. A brief clinical interview will be conducted and recorded for all laboratory abnormalities not present at baseline to provide context, i.e., new-onset anemia tied to increased diarrheal episodes, etc. Serum calcium, potassium, and sodium; ɣ-glutamyl transferase (GGT); and blood urea nitrogen (BUN) to creatinine ratio (BUN:Cr) will also be collected to monitor electrolyte balance and provide additional measures of liver and kidney function, respectively.

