### Participant timeline {13}

The flow of participant involvement and descriptions of study visit procedures are described in Fig. 1. Participants will be screened by phone to determine initial eligibility. Within 30 days of initial eligibility confirmation, participants will complete an in-person clinical screening visit to further confirm eligibility. If the candidate remains eligible, they will be invited to complete baseline and randomization visits within 30 days of screening. All additional visits will occur biweekly for 8 weeks and follow the procedure flow according to Fig. 1 and Table 3.

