## Statistical methods

### Statistical method outcomes {20a}

Laboratory measures will be analyzed first with descriptive statistics including mean, median, and standard deviation. Distributions will be tested for skew and transformed (e.g., natural log) as needed to reduce skew on subsequent analyses. If distributions indicate substantial non-normality that cannot be modified with transformation, non-parametric tests (e.g., Wilcoxon rank-sum) will be used.

In addition, the frequency of new, clinically significant laboratory abnormal values as outlined above will be monitored by the DSMB. The percentage of these new abnormal values per reference ranges will be reported at each time point and compared between groups by Fisher’s exact test. Assessment for changes in the distribution of each parameter will be presented as means and confidence intervals (CI) within and between groups. The significance of differences will be compared using 2-sided, unpaired *t*-tests if normally distributed and a non-parametric Wilcoxon rank-sum test of mean values between groups if non-normally distributed. Overall increases and decreases in laboratory parameters will be tested using linear mixed ANOVA with time point as a repeated factor, potentially suggestive of cumulative toxicity if trending in a clinically deleterious direction. All factors will be considered significant if *p* < .05.

Clinical activity will be measured through the CDAI. A score >150 is considered *clinically active* and is an eligibility criterion. Changes in score from baseline between groups will be compared within groups using two-sided, unpaired *t*-tests at each interval with the primary outcome as a change in value from baseline to closeout, whereas within-group changes will be compared using two-sided, paired *t*-tests. Non-parametric Wilcoxon rank-sum test of mean values between groups will be used if data are non-normally distributed.

Measures within the PROMIS-29 v.2.0 questionnaire include seven validated subscales, i.e., physical function, anxiety, depression, pain intensity, pain interference, sleep disturbance, and social interaction. Analyses will be performed by calculating descriptive statistics of mean, median, and mode of reported *T*-scores and overall PROMIS-29 questionnaire and each subscale. Welch’s *t*-test will be used to test the differences in scores between groups with *p* < .05 considered significant.

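### A laboratory abnormality first seen at week 8 can be confirmed only after dosing has ended; if the between-arm count uses confirmed events only, reversible XN effects at the longest exposure can go uncounted

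*Protocol article*

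**What the plan says.** Outcomes {12} in the protocol article places a general condition on new-onset laboratory abnormalities: they are "confirmed with repeat testing at the following clinical visit or as soon as possible following closeout, as applicable". It then gives a rule for each type of measure:

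- **Anemia:** three joint conditions, the third being that "values remain abnormal with repeat testing within 2 weeks".
- **Liver tests:** two conditions, namely outside the laboratory's range and that the values "represent a 25% deviation from previously observed values". There is no repeat condition of their own.
- **Creatinine and eGFR:** a change of more than 20% from baseline. There is no repeat condition of their own.

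On timing, participants are "randomized to either 24 mg encapsulated XN per day or placebo and followed for 8 weeks" (Abstract, Methods). Participant timeline {13} states that "All additional visits will occur biweekly for 8 weeks". Adherence is "formally assessed at the week 4 and closeout visits by capsule count" (section {11c}). No scheduled visit follows week 8.

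For the analysis, Statistical method outcomes {20a} refers back to the definitions of clinically significant abnormality and continues: "The percentage of these new abnormal values per reference ranges will be reported at each time point". The groups are compared by Fisher's exact test. The article does not say how a week-8 abnormality that is normal on its later repeat is counted.

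**The concern.** The purpose of a confirmation rule is to remove spurious values, and it does so fairly if the repeat is taken under the same conditions at every visit. Here the conditions change at the last visit. A value first abnormal at week 2, 4 or 6 is repeated while capsules are still being taken. A value first abnormal at week 8 is repeated afterwards.

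The two arms are not affected alike. Noise and passing illness can resolve before the repeat in either arm. An abnormality that XN causes, and that resolves because XN was stopped, can occur only in the XN arm. Resolution on withdrawal fits a drug cause, yet under a confirmed-only count it would cancel the event.

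The comparison at stake matters to the trial. Safety is hypothesised in terms of the frequency of laboratory abnormalities or adverse events (Hypotheses), and the sample size rests on the proportion of participants who have them (Sample size {14}). Week 8 is also where any effect that builds with exposure would be most visible.

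**Working it through.** **Step 1. When each repeat is taken.**

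| First abnormal at | Repeat under the rule | Dosing at repeat |
|---|---|---|
| Week 2 | Week 4 visit | Continuing |
| Week 4 | Week 6 visit | Continuing |
| Week 6 | Week 8 visit | Through week 8 |
| Week 8 | After closeout | Scheduled dosing over |

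The last row is inferred from 8 weeks of dosing, no later visit and the capsule count at closeout. Only anemia has a time limit for the repeat (2 weeks).

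**Step 2. The plan's own sample size.** No base rate is given. With 5% vs 55%, two-sided α 0.05 and 80% power (pooled χ², no continuity correction), the mean proportion is 0.30 and

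n = [1.96·√(2·0.30·0.70) + 0.8416·√(0.05·0.95 + 0.55·0.45)]² / 0.50²
= [1.270 + 0.457]² / 0.25 = 11.9, so 12 per arm.

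24/(1 − 0.25) = 32. Both stated figures reproduce at a low base rate (25% vs 75% would need 15 per arm). The confirmation rule does not enter this calculation.

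**Step 3. How many first events fall at week 8.** The documents give no onset rates, so these are assumptions. Let R be the risk of a first abnormality by week 8 in the XN arm, over four visits.

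- *Constant per-visit risk:* P(first at week 8) = (1 − R)^0.75 − (1 − R).
- *Per-visit risk rising 1:2:3:4:* solve (1 − c)(1 − 2c)(1 − 3c)(1 − 4c) = 1 − R for c. Then P(first at week 8) = (1 − c)(1 − 2c)(1 − 3c)·4c.

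| R | Constant: P | Share of first events | Expected in 12 | Rising: P | Share of first events | Expected in 12 |
|---|---|---|---|---|---|---|
| 0.30 | 0.065 | 21.8% | 0.8 | 0.109 | 36.5% | 1.3 |
| 0.40 | 0.082 | 20.4% | 1.0 | 0.140 | 35.0% | 1.7 |
| 0.50 | 0.095 | 18.9% | 1.1 | 0.167 | 33.3% | 2.0 |

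These are events exposed to the off-product repeat. The expected loss is this number times the fraction that are drug-caused and normal again by the repeat. If that fraction is one half, the loss is about 0.4 to 1.0 event.

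**Step 4. What a loss could do at 12 per arm.** Two-sided Fisher p-values for participants with any event during the trial:

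- 5 vs 0: 0.037; 4 vs 0: 0.093.
- 7 vs 1: 0.027; 6 vs 1: 0.069.

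These pairs were chosen at the boundary of significance. They show that one event can matter, not that it usually will. Section {20a} compares at each time point. With only 0.8 to 2 XN events expected at week 8, that single-visit test would rarely be significant anyway (2 vs 0 gives p = 0.48), so the loss would show mainly in the reported percentage.

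**Step 5. Effect on power for a participant-level count.** Let s be the share of the excess XN events first seen at week 8, and r the fraction of those that reverse before the repeat. The counted excess is 50·(1 − s·r) points. With true rates of 5% vs 55% and 12 per arm, exact Fisher power is:

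| s·r | Counted excess (points) | Power |
|---|---|---|
| 0 | 50 | 69% |
| 0.125 | 43.75 | 56% |
| 0.25 | 37.5 | 42% |

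With s at the top of the Step 3 range (0.365), s·r = 0.25 needs r = 0.25/0.365, about 0.68. The last row is therefore a demanding case.

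**The case against.** Four arguments weigh against the point.

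1. **Persistence is not a stated condition for most measures.** Only anemia lists it. For liver tests, creatinine and eGFR it comes from a parenthesis on how abnormalities are reviewed, and the article never says that an unconfirmed value is discarded. This stands. It is why the conclusion is conditional on the count using confirmed events.

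2. **The analysed frequency may not require confirmation.** Outcomes {12} also promises the frequency of new-onset or worsening values at each visit without mentioning a repeat, and section {20a} speaks of values outside reference ranges. But {20a} also refers back to the definitions that include the repeat. The text supports both readings, and that needs settling.

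3. **Week-8 toxicity is seen elsewhere.** The named primary endpoint for laboratory values is mean change to week 8, and the mixed model looks for trends over time. Both use the week-8 value as measured. New abnormalities also lead to a recorded interview. A reader might infer that week-8 toxicity disappears from the safety assessment; these provisions show that it does not. A mean can still hide a few individual elevations, which the count is there to catch.

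4. **The rule also removes non-drug events.** Transient abnormalities can resolve in either arm, so it does not follow that most of the removed events come from the XN arm. Only the drug-caused, quickly reversible part is differential, and no figure in the article says how large it is.

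The article condenses a fuller protocol, which may say how unconfirmed closeout values are classified. The timing of the repeat, however, is fixed in the outcome definition shown here.

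**Conclusion.** The concern holds in a limited form. As written, only abnormalities first seen at week 8 are confirmed after scheduled dosing has ended. If the between-group count is restricted to confirmed events, XN-caused abnormalities that reverse on stopping can be lost, and only from the XN arm. The direction is toward finding XN safe.

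The size cannot be derived from the documents. The 19–37% range is the share of first events that fall at week 8 under assumed risks of 30–50%, and should not be read as the share lost. It corresponds to about 0.8 to 2 XN participants in 12, and the loss reaches that number only if every such event is drug-caused and has reversed by the repeat. Mean change to week 8 and the mixed model are untouched. This is worth correcting before unblinding, but it does not invalidate the safety assessment.

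**What to change.** Apply one rule at all visits. Compare, by arm, the proportion of participants who meet the stated thresholds in two ways: without requiring confirmation, and with it. State that a normal repeat taken off product after closeout describes resolution and does not remove a week-8 event from the count. State also which of the two counts the Fisher comparison in section {20a} uses.

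Dropping confirmation at week 8 alone is not advisable: that visit would then no longer be comparable with weeks 2, 4 and 6. Showing both counts at every visit avoids this.

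The cost is a change of wording and one additional tabulation of data already collected, with no extra visit or sample. The downside is small: some spurious unconfirmed values enter the first count, expected equally in both arms.

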#### Hypotheses

We hypothesize 24 mg/day of XN will be safe and tolerable in an adult population with active CD over an 8-week period. This will be supported by observing no greater than a 50% greater frequency in differences of laboratory abnormalities or adverse events in the XN group. We also hypothesize XN will improve the clinical activity and reduce inflammatory biomarker concentrations in CD, demonstrate a metabolite profile different than that of healthy adults, and generate a specific gut microbiome signature. These comparisons will be achieved by measuring data against that from the phase I clinical trial of the same interventional product and period.

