The primary endpoint for laboratory values and vital sign measurements will be mean change from baseline to week 8, with changes also compared between groups from baseline to each additional follow-up visit (i.e., 2, 4, and 6 weeks). The frequency of new-onset or worsening laboratory values will be reported within groups throughout the trial at each biweekly visit. AEs and event severity will be reported as new-onset or worsening events spontaneously and at each biweekly visit. Together, these outcomes will provide a profile of safety and tolerability of 24mg XN for 8 weeks compared to placebo.

Secondary and exploratory outcomes include clinical disease activity, systemic inflammation (e.g., IL-10), intestinal permeability (e.g., intestinal fatty acid binding protein) and endotoxemia (e.g., LPS), platelet function, stool microbiome and bile acid composition, and the metabolic profile of XN in humans over 8 weeks. Each measurement will be collected at every biweekly clinical visit and compared between groups as mean change from baseline within groups and compared between groups at each follow-up visit. The primary endpoint for each secondary and exploratory outcome will be considered exploratory and reported as mean change within groups at week 8 from to baseline and compared between groups at each follow-up visit. The measurements to support these outcomes are outlined in Table 1.

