### Sample size {14}

A sample size of at least 12 participants per group provides 80% power to detect ≥50% difference in the proportions of participants experiencing laboratory abnormalities or adverse events at a threshold of *α* = .05 by *χ*^2^ test. This sample size, at *n* = 12 per arm, provides >90% power using 2-sided *t*-tests to detect a mean change of 0.25–0.5pg/mL in TNF-α in the treatment arm according to preliminary data from previous pilot studies. Accounting for attrition up to 25%, we will randomize up to 32 participants. Attrition during the phase I trial was 10% [15].

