### Adverse event reporting and harms {22}

Adverse events will be assessed and graded according to severity at each biweekly clinical visit beginning at the baseline visit, as well as accepted via spontaneous report. Self-reported adverse events will be administered by verbal query through a standardized multi-system questionnaire based on the National Cancer Institute’s Common Technology Criteria for Adverse Events v4.0. Adverse events reported between study visits will be termed “spontaneous adverse events” and graded in a similar manner according to self-reported adverse events according to severity and duration. If an adverse event is of moderate or greater severity, the study team will coordinate with the patient’s physician and develop and document a response or monitoring plan.

Adverse events, both self-reported and spontaneous, will be detailed according to severity and length of duration and compared between groups. The presence of symptoms at baseline will inform the attributability of any symptom to the intervention. Worsening or new-onset symptoms after baseline will be considered potentially attributable to the intervention and will be determined according to prevalence in each group and a case-by-case basis by the study team and DSMB.

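### The safety hypothesis and sample size rest on the proportion of participants with a laboratory abnormality or AE, but that proportion is neither the named primary endpoint nor analysed as sized

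*Protocol article*

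**What the plan says.** **Hypotheses.** Safety and tolerability will be judged on frequency: "This will be supported by observing no greater than a 50% greater frequency in differences of laboratory abnormalities or adverse events in the XN group".

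**Sample size {14}.** Twelve per arm is said to give "80% power to detect ≥50% difference in the proportions of participants experiencing laboratory abnormalities or adverse events", at α = .05 by chi-square test. Allowing for 25% attrition, up to 32 are randomized.

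**Outcomes {12}.** The primary outcomes are laboratory measures, vital signs and AEs. The section defines clinically significant changes in liver tests, anemia, creatinine and eGFR, with repeat testing to confirm new abnormalities. It then fixes the endpoint: "The primary endpoint for laboratory values and vital sign measurements will be mean change from baseline to week 8". Changes at weeks 2, 4 and 6 are also compared, and abnormality frequencies are reported within groups at each visit.

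**Statistical method outcomes {20a}.** Percentages of new abnormal laboratory values are compared between groups by Fisher's exact test at each time point. Mean changes are compared by unpaired t-test or Wilcoxon rank-sum test.

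**Adverse event reporting and harms {22}.** "Adverse events, both self-reported and spontaneous, will be detailed according to severity and length of duration and compared between groups". No participant-level measure or test is named.

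**The concern.** The protocol asks one question and names an endpoint that answers another. The hypothesis and the sizing ask how many participants on each arm have a laboratory abnormality or an AE. The named endpoint asks how far the average laboratory value or vital sign moves by week 8. No result on the second scale can confirm or refute a statement about the first.

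At stake is whether the trial reports a direct answer to its own safety hypothesis. As written, the reader would receive mean changes, a series of visit-wise laboratory percentages and an AE comparison of unspecified form. None of these is the quantity for which 12 per arm was justified, and they cannot simply be added up: one participant may appear at several visits, or have both a laboratory abnormality and an AE.

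**Working it through.** **1. The sections side by side**

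| Section | Quantity | Unit and period | Laboratory | AEs | Test |
|---|---|---|---|---|---|
| Hypotheses | frequency of abnormalities or AEs | 8 weeks | yes | yes | none named |
| Sample size {14} | proportion with an abnormality or AE | participant | yes | yes | chi-square |
| Outcomes {12}, named endpoint | mean change | group mean, week 8 | yes (and vital signs) | no | t-test or Wilcoxon in {20a} |
| Statistical methods {20a} | percentage of new abnormal values | each time point | yes | no | Fisher |
| AE reporting {22} | severity and duration | not stated | no | yes | none named |

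Only the first two rows combine laboratory abnormalities and AEs. Neither is carried into an endpoint definition or an analysis.

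**2. The plan's own sample size**

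Inputs from Sample size {14}: 80% power, α = .05 (taken as two-sided), a 50% difference and 25% attrition. Assumptions: the 50% is an absolute difference, and the placebo rate p₁ varies, because the protocol gives none.

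n per arm = [1.96·√(2p̄(1−p̄)) + 0.8416·√(p₁(1−p₁)+p₂(1−p₂))]² / (p₂−p₁)²

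At 5% vs 55%, p̄ = 0.30:
- 1.96·√0.42 = 1.270
- 0.8416·√0.295 = 0.457
- (1.270 + 0.457)² / 0.25 = 11.9, so 12 per arm

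The stated figure reproduces. Attrition also reproduces: 24 / (1 − 0.25) = 32.

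Read instead as a relative 50% increase, 12 per arm does not reproduce. A rise from 40% to 60% needs 97 per arm (power 0.16 at 12), and a rise from 20% to 30% needs 294 (power 0.08).

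**3. The same difference under the planned test**

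Fisher power is by exact enumeration. Chi-square is the normal approximation without continuity correction; its first row uses 0.1% vs 50.1%.

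| Placebo vs XN (assumed) | n per arm for 80%, chi-square | Power at 12, chi-square | Power at 12, Fisher | Power at 16, Fisher |
|---|---|---|---|---|
| about 0% vs 50% | 11 | 0.855 | 0.81 | 0.96 |
| 5% vs 55% | 12 | 0.80 | 0.69 | 0.855 |
| 10% vs 60% | 14 | 0.76 | 0.64 | 0.79 |
| 25% vs 75% | 15 | 0.71 | 0.61 | 0.74 |

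The 80% claim therefore depends on an unstated placebo rate and on a test that the analysis section does not name for these percentages.

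**4. Mean change**

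Twelve per arm gives power 0.80 for a standardized difference of 1.2 by two-sided t-test, the figure in {20a}. That sentence stands in the paragraph on secondary and tertiary outcomes. It shows what a mean comparison can detect, but does not connect a mean to the hypothesis.

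**The case against.** The strongest reply is that frequency is not ignored. AEs are listed among the primary outcomes, laboratory abnormality percentages are tested between arms, and AEs are compared between groups. The mean-change endpoint is limited to laboratory values and vital signs, and the section says the outcomes together form a safety profile. All of this stands. A reader might infer that no planned analysis measures frequency at all; the protocol does not support that. What is missing is the combined participant-level proportion.

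A reader might also infer that transient abnormalities vanish. They do not: weeks 2, 4 and 6 are compared too, and a repeated-measures model is planned.

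Two further arguments are tempting but fail.

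- **A mean hides a few severe cases, so a proportion would detect them.** At 12 per arm it would not. Three of 12 against none gives two-sided Fisher p = 2 × 220/2024 = 0.22. Significance needs five against none: 2 × 792/42504 = 0.037. The advantage of the proportion is that it matches the hypothesis and shows the affected participants with their uncertainty, not that it has more power.
- **AEs would saturate both arms, so a 50-point difference could not occur.** With an assumed 30–40% reporting per visit, independent over four visits, 1 − 0.7⁴ = 76% to 1 − 0.6⁴ = 87% would have at least one event. The protocol supplies neither the rates nor the independence. With an assumed within-person correlation of 0.5–0.7 the cumulative rate is 42–63%, leaving room for 37–58 points.

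Finally, an article may leave an AE test or a pooling rule to the full protocol or SAP. That would excuse missing detail. It does not excuse a named primary endpoint that differs from the sized one, since the article itself fixes both.

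**Conclusion.** The point holds as a mismatch between sections. The hypothesis and sample size concern a participant-level proportion; the named endpoint for laboratory values and vital signs is a mean change; and the planned frequency analyses cover only components of that proportion. The composite over 8 weeks is neither named as primary nor analysed as sized.

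This conclusion comes from the text and needs no assumption. The numbers in support do. The stated 12 per arm is not an arithmetic error: it reproduces for an absolute 50-point difference at a placebo rate near 5%. Across the assumed placebo rates of about 0% to 25%, Fisher power at 12 per arm runs from 0.81 down to 0.61.

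The change should be made, because without it the trial does not directly report the quantity on which its safety hypothesis stands.

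**What to change.** - **Outcomes {12} and Statistical method outcomes {20a}:** make the primary safety analysis the proportion of participants with at least one confirmed clinically significant laboratory abnormality, as already defined, or at least one new-onset or worsening AE, at any time from first dose through week 8. Report it by arm with the between-arm difference and an exact confidence interval.
- **Population:** count all dosed participants. Section {20c} makes all analyses per protocol, so it needs an exception here. Otherwise participants withdrawn for AEs or laboratory values under {11b} may drop out of the safety result.
- **Additional summary:** show the same proportion with AEs restricted to moderate or greater severity. This should not replace the main definition, because tolerability is part of the objective and mild events bear on it.
- **Supportive:** keep mean changes and visit-wise percentages.
- **Sample size {14}:** align the test with the one used, and state the assumed placebo rate and whether the 50% is absolute. Word the Hypotheses section to match.

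The cost is a wording amendment, best made before group assignments are revealed; all data are already collected. There are two small downsides: mean change becomes supportive, and power for the proportion at 12 per arm depends on a placebo rate that has yet to be stated.
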